### Clustered randomised clinical trial

Participating general practices are randomised over 3 groups (figure 1). GPs in group 1 are instructed to order blood tests immediately at the first consultation. Those in group 2 are instructed to restrict blood test ordering to patients with complaints persisting after four weeks. GPs in group 3 are also instructed to try and postpone test ordering, but they also participate in a quality improvement strategy that supports them in postponing test ordering for patients with unexplained complaints. The study design includes two sub-studies. The first is a diagnostic study comparing patients from group 1 (immediate test ordering) with patients from groups 2 and 3 (4 weeks of watchful waiting). The second is a quality improvement study, comparing group 2 (instruction to postpone test ordering) with group 3 (instruction to postpone test ordering plus quality improvement strategy) in terms of the actual postponement of test ordering.

**Figure 1 F1:**
[figure not shown]
Randomisation scheme.

The reason why we decided to randomise general practices instead of patients or individual GPs is that we assumed there would be contamination, for three reasons. Firstly, it is not possible for GPs to selectively use the communication skills they have learnt during the quality improvement strategy in one patient and fall back to their previous behaviour in the next patient. Secondly, in group practices, patients are sometimes seen by different colleagues at different appointments. If these GPs are in different intervention arms, this may bias the results. Thirdly, patients of different GPs within one practice may exchange experiences about the scientific research project they participate in. The randomisation procedure is carried out separately for the two regions where the participatinjg university departments are located. To achieve allocation concealment, study groups are assigned to GPs by a random number seed computer program that randomises in blocks and is operated by an experienced research assistant.

### Procedure

If, after history taking and physical examination, a patient is considered to have unexplained complaints and gives informed consent, the GP enrols the patient in the study. Depending on the GP's study arm, blood test ordering or a 4-week watchful waiting policy is suggested to the patient. All patients are asked to return to the GP if complaints do not disappear within 4 weeks. If patients return, blood tests are ordered for every patient, irrespective of GPs' study arm. This means that patients in group 1 are then tested for the second time and patients in groups 2 and 3 for the first time.

All tests are performed at the regional laboratory, according to local standard operating procedures and using the local reference values.

Patient follow-up ends at 12 months after the initial consultation.

### Power calculation

Based on previous research, we estimated that approximately 2 percent of patients will eventually be diagnosed with serious pathology.[16] We estimated that 100 patients with pathology will be needed to allow valid conclusions, which means that 5000 patients should be included in the study. Dutch GPs see approximately 500 patients a month, of whom 1–5% are estimated to have unexplained complaints. This means that each GP could on average include 180 patients in one year. These figures mean that we need 27 GPs to participate. Assuming a patient refusal rate of approximately 50 percent, 54 GPs need to be recruited. A total of 5000 patients (approximately 1700 in each study group) would also be sufficient to determine the costs and effects of the quality improvement strategy with enough precision.

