* T0 for patients randomised to group 1, T1 for all patients but only if they revisit their GP

^# ^T1 is the time point to measure a follow-up visit by the patient 4 weeks after inclusion. If a patient does not return to the GP, a questionnaire is sent by mail after 6 weeks. This time point is indicated as T1.5.

Most questions in the questionnaires have been formulated by the research team, based on topics found in the literature. Quality of life is measured by the RAND SF36, together with the thermometer of the Euroqol questionnaire. Both are widely used and have been validated extensively.[24-26]

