### Data analysis

#### Primary outcome measures of the diagnostic intervention

The first primary outcome is the accuracy and added value of blood tests in detecting serious pathology (per test and in combinations relevant to general practice), related to and in addition to signs and symptoms. Serious pathology is defined as pathology requiring treatment. The second primary outcome is the effect of a 4-week postponement of test ordering on the blood test characteristics.

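### The 100 pathology cases behind the 5000-patient target are counted over everyone enrolled, not over those tested; about 33 are tested at presentation under the group 1 instruction

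*Protocol article*

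**What the plan says.** All references are to the protocol article.

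- **Power calculation.** The prevalence assumption is that "approximately 2 percent of patients will eventually be diagnosed with serious pathology". The sample size follows from it: "We estimated that 100 patients with pathology will be needed to allow valid conclusions, which means that 5000 patients should be included". The same section puts about 1700 patients in each study group. It gives no other numerical criterion for the diagnostic study.
- **Clustered randomised clinical trial.** The diagnostic sub-study sets group 1 (immediate testing) against groups 2 and 3 together (four weeks of watchful waiting).
- **Measurements, footnote to Table 3.** Test results are available at "T0 for patients randomised to group 1, T1 for all patients but only if they revisit their GP".
- **Procedure.** When patients come back at 4 weeks, "patients in group 1 are then tested for the second time and patients in groups 2 and 3 for the first time".
- **Watchful waiting for 4 weeks.** GPs in groups 2 and 3 may order tests at once where waiting is not feasible. The expected share is not given.
- **Primary outcome measures of the diagnostic intervention.** The first outcome is the accuracy and added value of the tests for serious pathology. For the other: "The second primary outcome is the effect of a 4-week postponement of test ordering on the blood test characteristics".

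**The concern.** A patient with pathology informs sensitivity only if there is a test result to set against the 12-month diagnosis. The calculation counts every enrolled case, whether tested or not. Under the testing schedule, one third of the cases are tested at presentation by instruction, and most of the rest are tested only if they come back. The section makes no allowance for the split into groups or for non-return.

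At stake is how far the 5000 patients can be trusted to support the diagnostic conclusions. A reader who takes the 100 cases at face value will expect estimates of sensitivity, and of its change with postponement, to be considerably more precise than the design can give.

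**Working it through.** **Inputs from the protocol article:** 2% prevalence, 100 cases, 5000 patients, three groups of about equal size (Power calculation); who is tested and when (Procedure; Table 3 footnote).

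**Assumptions, because the document gives no figures:** sensitivity 80%; specificity 80%; return share *r* among cases in groups 2 and 3, from 30% to 100%; independent observations (no clustering).

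**1. The plan's figure.** 100 / 0.02 = 5000. It reproduces exactly. 5000 / 3 = 1667, consistent with the rounded 1700.

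**2. Cases by group.** 100 / 3 = 33.3 in group 1 (34 if 1700 patients are used) and 66.7 in groups 2 and 3.

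**3. Precision of one sensitivity.** Half-width = 1.96 × √(0.8 × 0.2 / cases).
- 100 cases: 7.8 points.
- 33 cases: 13.6 points.

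**4. Immediate against postponed testing.** Half-width = 1.96 × √(0.16 / 33.3 + 0.16 / (66.7 × *r*)).

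| Return share *r* (assumed) | Cases first tested at 4 weeks, groups 2 and 3 | Group 1 at presentation plus these | 95% half-width of the difference in sensitivity |
|---|---|---|---|
| 30% | 20 | 53 | 22.2 points |
| 50% | 33 | 67 | 19.2 points |
| 70% | 47 | 80 | 17.8 points |
| 100% | 67 | 100 | 16.6 points |

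The pooled count reaches 100 only in the last row, and only by adding the two sets of results that the second primary outcome is meant to compare.

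**5. Early testing in groups 2 and 3.** If 20% of their cases were tested at presentation (assumption), cases tested at presentation would be 33.3 + 0.2 × 66.7 = 46.7. The Table 3 footnote lists presentation results for group 1 only, so it is unclear whether such results would be used.

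**6. Group 1 retests at 4 weeks.** If the same share *r* applies in group 1, cases with a 4-week result over all three groups are 100 × *r*. This reaches 100 only if every case in every group returns.

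**7. Specificity, for contrast.** Non-cases: 1667 − 33, about 1633, in group 1. In groups 2 and 3 at 30% return among non-cases: 0.3 × 3267 = 980. Half-width of the difference = 1.96 × √(0.16 / 1633 + 0.16 / 980) = 3.2 points.

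**The case against.** Several points on the other side stand and limit the concern.

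- **No requirement per outcome is written down.** The 100 is stated for the study as a whole. A reader might infer that the plan demands 100 cases for each diagnostic outcome and breaks its own rule; the text does not say that. Nor does the first primary outcome restrict itself to tests at presentation. What remains is that 100 is the only diagnostic criterion given, and it is met only across all groups combined.
- **Groups 2 and 3 are not tested solely on return.** Early testing is allowed, and a case tested early is a tested case. This adds to the count by an unknown amount.
- **Low return among cases is not established.** The Blood test ordering section expects most complaints to be self-limiting, but it also expects a higher probability of pathology in those whose complaints persist. Cases may therefore be concentrated among returners, and values near 100% belong in the range. Even at 100% the contrast is 33 against 67.
- **Sensitivity is only part of the second outcome.** The stated rationale for postponement is fewer false positives. Specificity rests on large numbers of non-cases, so it would be wrong to conclude that the whole outcome is imprecise.
- **Group 1 retests add information.** They supply further 4-week cases and within-patient comparisons, which the unpaired calculation leaves out.

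The journal article is also a condensed account, and sizing per comparison may exist in the full protocol. The point here is therefore not the absence of detail. It is that the adequacy the article does state does not follow from its own testing schedule.

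**Conclusion.** The concern holds as a matter of stated adequacy. The division of 100 by 2% is correct, so this is not an arithmetic error; the population over which cases are counted is the problem. About 33 cases are tested at presentation in group 1, and at most 67 stand on the other side of the comparison.

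For sensitivity, a single estimate in group 1 is about 1.7 times as wide as the 100-case figure suggests (13.6 / 7.8). The immediate-versus-postponed difference carries a half-width of roughly 17 to 22 points. These widths depend on the assumed 80% sensitivity and, for the difference, on the assumed return share; clustering by practice is ignored. The count of 33 needs only the plan's 2% and equal groups.

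A reader might also infer that a non-significant difference will be taken as proof that postponement changes nothing. The article plans no such reading. The precision above is a reason to guard against it, not evidence that it is intended. The point should be fixed, but it does not invalidate the design.

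**What to change.** In the Power calculation section, replace the single count with expected tested cases per analysis set, each labelled separately:

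- about 33 at presentation in group 1;
- 67 times the return share at 4 weeks in groups 2 and 3, shown over a range up to 100%;
- any cases tested early in groups 2 and 3, with a statement of whether their results enter the accuracy analysis;
- group 1 retests at 4 weeks.

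Give the resulting interval widths for sensitivity, and make clear that 5000 patients do not yield 100 tested cases for each diagnostic outcome. Report the effect of postponement on sensitivity as an estimate with its confidence interval.

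The Cooperation section says that data collection has ended, so the sample is fixed. The change is to the text and the reporting; no extra patients are needed. The cost is a less favourable stated precision.

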### Diagnostic intervention at patient level

#### Selection of blood tests

Members of an expert panel including GPs and hospital specialists (n = 20) have been individually asked to propose tests which they regarded as useful diagnostic tools in general practice for each of the 5 complaints. All tests mentioned at least twice were included in a complaint-specific set of tests (table 1). If not already included in the set, the four tests recommended in the NHG guideline (glucose, ESR, TSH and Hb) were added. In addition, iron parameters (transferrin saturation (TS) and ferritin), anti-endomysium and carbohydrate deficient transferrin (CDT) were added as indicators of haemochromatosis, celiac disease and alcohol abuse respectively. These three diseases can lead to unexplained complaints, are frequently missed by GPs according to the literature and should be demonstrable with the above blood tests. The diagnostic accuracy of these tests in patients presenting with unexplained complaints in general practice has, however, not yet been established.[12,17-20]

**Table 1 T1:** Sets of laboratory tests per complaint

	**Fatigue**	**Abdominal complaints**	**Musculo- skeletal complaints**	**Weight changes**	**Itch**
Alkaline Phosphatase (AF)	x	x		x	
Alanine aminotransferase (ALAT)	x	x		x	x
Amylase		x		x	
Anti-endomysium		x		x	
Aspartate aminotransferase (ASAT)	x	x		x	
Bilirubin					x
Erythrocyte sedimentation rate (ESR)	x	x	x	x	x
Carbohydrate-deficient transferrin (CDT)	x	x		x	x
Creatinin kinase (CK)			x		
Creatinin	x	x	x	x	x
C-reactive protein (CRP)		x			
Differentiated leukocyte count	x	x		x	x
Eosinophils					x
Ferritin	x	x	x	x	
Gamma glutamyl transferase (GGT)	x	x		x	x
Glucose	x	x	x	x	x
Haemoglobin (Hb)	x	x	x	x	x
Potassium (K)	x		x		
Latex fixation test			x		
Lactate dehydrogenase (LDH)	x			x	
Leukocyte count	x	x		x	x
Monosticon	x				
Total IgE		x			x
Thyroid stimulating hormone (TSH)	x	x	x	x	x
Transferrin saturation (TS)	x	x	x	x	
Urea					x
Uric acid			x		
**Total number of tests**	**17**	**18**	**11**	**17**	**14**

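### The 100 pathology cases behind the sample size are counted over all three groups, but only about 33 to 34 of them are tested at presentation by design

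*Protocol article*

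**What the plan says.** The Power calculation section of the protocol article expects that "approximately 2 percent of patients will eventually be diagnosed with serious pathology" and concludes that "100 patients with pathology will be needed to allow valid conclusions, which means that 5000 patients should be included in the study". It spreads these patients over three groups: "A total of 5000 patients (approximately 1700 in each study group").

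The groups are tested at different times. Under Clustered randomised clinical trial, "GPs in group 1 are instructed to order blood tests immediately at the first consultation", whereas "Those in group 2 are instructed to restrict blood test ordering to patients with complaints persisting after four weeks"; group 3 is also told to postpone. Under Procedure, every patient who returns at 4 weeks is tested, which is a second test for group 1 and a first test for groups 2 and 3. The footnote to Table 3 says when test results exist: "T0 for patients randomised to group 1, T1 for all patients but only if they revisit their GP".

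The Data analysis section defines what the diagnostic sub-study must deliver: "The first primary outcome is the accuracy and added value of blood tests in detecting serious pathology". This is wanted both for single tests and for sets of tests used together. The second primary outcome is the effect of the 4-week postponement on the test characteristics. The tests come in sets by complaint (Selection of blood tests, Table 1): "All tests mentioned at least twice were included in a complaint-specific set of tests", with a few further tests added.

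**The concern.** Sensitivity can be estimated only from patients who have both the disease and a test result. The power section sets a requirement in diseased patients and meets it by counting all of them, whether or not the design gives them a test. Two thirds of the expected cases are in groups where, by design, there is no test at presentation and a test at 4 weeks only on return. The section does not split the 100 by time of testing and does not mention the return rate.

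The loss falls on sensitivity, because non-diseased patients are plentiful in every group. Sensitivity is also what supports the expectation, stated in the Abstract, that serious pathology will not be missed. A reader who takes the 100 at face value will expect narrower intervals than the design can give, both for accuracy at presentation and for the comparison of immediate with postponed testing.

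**Working it through.** **Inputs from the protocol article.** Prevalence 2%, 100 cases, 5000 patients and about 1700 per group (Power calculation); three groups (Clustered randomised clinical trial); timing of tests (same section, Procedure, Table 3 footnote); test sets (Table 1). **Assumptions, not in the document:** sensitivities of 80% and 50%, and r, the share of cases who return and are tested at 4 weeks.

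**1. The plan's own figure.** 100 / 0.02 = 5000, reproduced exactly. 5000 / 3 = 1667, consistent with about 1700 per group.

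**2. Cases tested at presentation.** 1667 × 0.02 = 33.3, or 1700 × 0.02 = 34. Groups 2 and 3 together hold 100 − 33.3 = 66.7 expected cases.

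**3. Cases tested at 4 weeks.** Groups 2 and 3 supply 67r. Returning group 1 patients are tested again, so over all groups the count is up to 100r. These retests are of patients already counted in step 2 and add no new cases.

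**4. Distinct cases with a test at either time: 33.3 + 66.7r.**

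| r | Groups 2+3 at 4 weeks | All groups at 4 weeks (up to) | Tested at either time |
|---|---|---|---|
| 0.25 | 17 | 25 | 50 |
| 0.50 | 33 | 50 | 67 |
| 0.75 | 50 | 75 | 83 |
| 1.00 | 67 | 100 | 100 |

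**5. Precision of sensitivity (Wilson 95% intervals).**

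- Near 80%: 26/33 gives 0.62 to 0.89; 80/100 gives 0.71 to 0.87.
- Near 50%: 16/33 gives 0.33 to 0.65 (half-width 16 points); 50/100 gives 0.40 to 0.60 (half-width 10 points).

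**6. Precision of the randomised comparison, group 1 against groups 2 and 3.** With the same sensitivity s in both, the half-width is 1.96 × √[s(1−s)(1/33 + 1/m)], where m = 67r.

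| r | m | s = 0.8 | s = 0.5 |
|---|---|---|---|
| 0.50 | 33 | ±19 points | ±24 points |
| 0.75 | 50 | ±18 points | ±22 points |
| 1.00 | 67 | ±17 points | ±21 points |

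This treats the two sides as independent, ignores clustering by practice, and does not use the paired results from group 1 retests. For illustration, a sensitivity of 0.6 against 0.8 with 33 against 67 cases (r = 1) has about 56% power at two-sided 0.05.

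**7. Table 1 recount.** There are 27 tests. Five are in all five sets: ESR, creatinine, glucose, Hb and TSH. Eight are in one set only: bilirubin, CK, CRP, eosinophils, latex fixation, Monosticon, urea and uric acid. So 27 − 5 = 22 tests are not run in every complaint and cannot draw on every case, even at r = 1. How cases divide over the complaints is not given, so no case count per test is calculated here.

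**The case against.** **The first primary outcome names no time of testing.** This stands. A reader might infer that this outcome rests on about 33 cases; the document does not say so. The figure of 33 to 34 applies to accuracy at presentation. With 4-week results added, the count is 33 + 67r.

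**Group 1 is retested on return.** This also stands. Postponed-test results can come from all groups, so 67r is the right count only for the randomised comparison. Paired results within group 1 could inform the second primary outcome, although cases already diagnosed from the first test may return less often.

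**The two sources can be combined.** A model with a timing term can use both, and Types of analysis already foresees repeated-measurements and multilevel methods. It would therefore be too strong to say that pooling is impossible. What fails is simple pooling without such a term: it assumes away the difference that the second primary outcome is meant to estimate, and the Background expects accuracy to be higher in persistent complaints. Signs and symptoms are recorded at the first visit in all patients, so that part of an added-value model can use all of the roughly 100 cases.

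**Early testing is allowed in groups 2 and 3.** It could add a few cases. They would be selected, their share is not given, and the Table 3 footnote schedules no first-visit results for them.

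**Overfitted models.** A reader might also infer that up to 18 tests will enter one model with 33 events. Nothing says so: 18 is the abdominal set only, and the text speaks of combinations relevant to general practice. Model size and optimism correction belong to the analysis plan, which is not shown.

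**The arithmetic is right, and 100 is tied to no precision target.** Both are true. The fault is in what is counted. Data collection has ended, so the remedy concerns claims and not recruitment.

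**Conclusion.** The point holds in this limited form: the power section's 100 cases do not all have a test result under the design in the same article. Accuracy at presentation has about 33 to 34 expected cases, a third of the stated requirement, and an interval of about 0.62 to 0.89 at a sensitivity near 80% where 100 cases would give 0.71 to 0.87. Over both time points the count reaches 100 only if every case in groups 2 and 3 returns. For 22 of the 27 tests it is lower still, to the extent that cases arise in complaints where the test is not run.

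The case counts rest on the protocol's own 2%, equal groups and testing as instructed. The intervals rest on assumed sensitivities, and everything after 4 weeks rests on r, which the article does not give.

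**What to change.** Rewrite the power section to state expected tested cases and confidence-interval widths separately for:

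- immediate testing: about 33 to 34 cases;
- postponed testing, over a range of r: 67r in groups 2 and 3, and up to 100r over all groups with group 1 retests;
- the immediate-versus-postponed comparison: 33 against 67r, saying whether paired group 1 results are used.

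Do not claim that 100 cases support per-test accuracy. If results from both time points are combined, include a term for time of testing. Label accuracy estimates for the 22 tests not run in all five complaints as exploratory.

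The cost is wording in the article and the analysis plan, with no extra patients. The downside is a less favourable stated precision and exploratory status for most of the individual tests.

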### Participants

The project is being carried out in a two regions in the Netherlands, one in the south and one in the west.

#### GPs

For logistic reasons, only GPs associated with certain laboratories for the handling of their test requests can participate in the trial. These laboratories are situated in the western (Haarlem, Almere) and southern (Sittard, Weert, Geldrop, Eindhoven, Helmond, Veldhoven, 's Hertogenbosch) regions. No further GP participation criteria were formulated.

